#### Self-perception

Thirty six questions are used to measure participant’s self-perception. The Sport Competences, Body Attractiveness and Physical Self-worth subscales from the Children’s Physical Self-Perception Profile (C-PSPP) is used to assess changes in the primary outcome measures: Physical self-concept [35, 36]. The Scholastic Competence, Social Competence and Global Self-worth subscales from the Self-perception Profile for Children (SPPC) are included to measure aspects of psychosocial well-being. The SPPC, developed by Susan Harter, is widely used and found to be valid and reliable [37–39]. All scales in the SPPC and C-PSPP are calculated as the mean of 6 items. Each item consists of two statements, which are scored on a four-point scale using a structured alternative format designed to reduce social desirability. Firstly, the pupil is asked to decide what kind of kid he or she is most like in each statement. E.g. “Some kids do very well at all kinds of sports, BUT other kids don’t feel that they are very good when it comes to sports”. Next, the pupil has to decide whether the selected description is “Really True for Me” or “Sort of True for me”. A score of 1 indicates the lowest perceived competence or adequacy, and a score of 4 reflects the highest level of competence or adequacy.

#### Socio-demographics

Four structured questions are used to determine the socio-demographic characteristics of the pupils. Furthermore, family social class is measured based on information on parental occupation. The information is coded into occupational social class I-V, economically active, or unclassifiable (VI), economically inactive (VII), unclassifiable (VIII), missing information (IX). Family social class is equal to the parent with the highest occupation social class [40].

#### Physical activity

Leisure time physical activity is assessed using two structured questions. Firstly, pupils are asked to choose from four statements denoting different levels of leisure time PA (e.g. engaging in organized sports several times a week or preferring sedentary activities e.g. playing with the computer and listening to music) [41]. Secondly, the pupils are asked how often they are physically active at a level that makes them breathe hard and fast and/or gets them sweating. This item is scored on a 6-point Likert scale from “Everyday” through “Never”. The frequency of physical activity during recess is measured with a single question using a 4-point Likert format ranging from “Several times a day” to “Rarely or never”. Lastly, the pupils are required to answer how often they walk or bike to school on a 4-point Likert Scale (“Everyday” to “Never”).

#### Self-efficacy

Measured using 8 questions. The scale uses a single factor 5-point Likert format and is an adapted version of an 8-item questionnaire previously developed for use with 5^th^, 6^th^ and 8^th^-grade girls (PASES) [42–44]. In accordance with Bartholomew et al. [45], the original wording is changed from an explicit focus on *leisure time* physical activity, to encompass self-efficacy regarding PA in general (leisure and school time). The pupils are asked to select how much they agree with eight statements ranging from “Disagree a lot” to “Agree a lot”. Each item is scored from 1 to 5, with a score of 1 indicating lowest self-efficacy.

#### Enjoyment

Is measured using seven negatively worded questions from the Physical Activity Enjoyment Scale (PACES). The scale uses a 5-point Likert format and is an adapted version of the 16-item version of PACES. This instrument has been validated for use with children and adolescents [46–51]. Pupils are asked to select how much they agree with seven statements relating to different feelings about physical activity (“Agree a lot” to “Disagree a lot”). Each item is scored from 1 to 5, with a score of 1 indicating lowest enjoyment. E.g. “When I am physically active…I feel bored”.

#### Perception of physical education (PE)

Five structured questions are used to measure the perception of PE in relation to the frequency of participation and involvement in, the motivation for and the enjoyment of PE. Each question is scored on a 4 or 5-point Likert scale.

#### School and general well-being

Information relating to psychological well-being and school physical and psychosocial environment is measured using 13 questions stemming from the Danish national survey of well-being in the school-aged population. These questions are implemented to enable comparison not only within the study sample but also with national distributions on these key elements.

#### Health-related quality of life (HRQoL)

Information relating to the participant’s perception of general well-being is measured using the KIDSCREEN-27 Quality of Life Questionnaire for Children and Adolescents [52] - The KIDSCREEN Group Europe 2006). This tool consists of 27 items on physical well-being (5 items), psychological well-being (7 items), autonomy and parent relationship (7 items), peer and social support (5 item), and school environment (5 items). Each item is scored on a 5-point Likert scale with a timeframe of one week. Higher scores indicate better HRQoL, e.g. “Thinking about the last week…Have you felt lonely?”

### Evaluating implementation

This part of the program evaluation considers the adoption, implementation and short-term maintenance of the intervention program according to the RE-AIM framework. The focus is on three levels of operation: the strategic level (school managers and coordination group CG), the operational level (educators) and the user/beneficiary level (the pupils).

At the *user/beneficiary level,* the main objective is to assess pupils’ experiences with the intervention components. Did they experience a change, and did the change increase their motivation for and participation in physical activities at school? There is a specific focus on pupils who are most at risk of experiencing a ‘vicious cycle’ in relation to physical activity at school. Pupils at two schools are especially closely followed by a researcher using ethnographic methods, taking part in everyday school life. Informal interviews are conducted, which are supported by focus group interviews with pupils and individual interviews with educators. Approximately 25–30 days of observation, 10 focus group interviews and interviews with 4 educators are conducted at the two selected schools. To increase the information on the user-level, class evaluations are conducted at the end of the study in one random class at each grade level at all 24 schools. The class evaluation collects the immediate experience of school PA for pupils at all schools and focuses on the four settings for PA included in the intervention program (Table 1).

At the *operational level,* the main objective is to assess the fidelity and feasibility of the intervention. Did the educators receive enough information about the intervention and were they able to conduct activities as intended? The evaluation focus’ on self-efficacy in relation to executing activity components, perceived relevance and educators experienced resistance from the pupils regarding intervention participation. Three times during the intervention period, educators are asked to fill in online questionnaires on issues like these. Additionally, a selected group of PE teachers at four intervention schools are more intensively followed - focusing on their practice of the PE lessons designed for this particular intervention program (Table 1). Finally, the research group is informed about general progress, barriers and successes in connection with the previously mentioned supervision visits to each school. At the meetings, the researchers follow PE classes, observe recess and in-class activities and engage in informal conversations with the educators.

At the *strategic level,* the main objective is to assess the context in which the educators are operating. Did the school managers and CG support the intervention program, and did they ensure a collaborative effort to make it a whole-school approach? School managers are interviewed as regards their role in both leading and managing the intervention, and the *CGs* participate in two meetings with the research team during the supervision visits. The meetings center on four statements related to the role of the CG:
*Well-being in school* is running fully as intended in our schoolOur colleagues are positive towards *Well-being in school*

*Well-being in school* is a priority at our school and receives adequate support from the school managementThe three bearing SDT-principles - competence, autonomy and relatedness – are evident for all involved as leading principles of *Well-being in school*.

The statements are visually presented via analog continuum scales and the CGs are asked to state the level of implementation by placing a mark on scales for each of the four statements. The rest of the meeting concerns the reasons for the level of implementation, and how the CGs can improve the current status. The individual ratings from the members of the CGs are summarized into one ‘Room For Improvement’ (RFI) score for each school.

### Statistical considerations

Sampling is school-based (cluster randomized) and individual respondents are therefore not independent. Some of the variances in measurements can be ascribed to class, school and surrounding environment [32]. This internal variation at school and class level was accounted for in the sample size calculations and will be accounted for in the effect analyses.

Based on baseline data from the pilot study, an intracluster correlation coefficient (ICC) was calculated for the primary outcome (mean of ‘physical self-worth’ from the Children’s Physical Self-Perception Profile) using ‘clustersampsi’ in STATA version 14 [53]. With a mean of 3.12, an SD of 0.70, a significance level of 0.05, a statistical power of 0.80, an ICC of 0.025 at school-class level, 72 classes from 12 schools on each arm and approximately 20 pupils in each class, it will be possible to detect a difference of 0.09. The mean of ‘physical self-worth’ should, therefore, be increased from 3.12 to 3.21 before a significant effect can be detected.

The effect of the intervention is tested using multilevel models adjusted for relevant, potentially confounding factors (e.g. baseline outcome measure, gender, age and family social class).

When testing the overall effectiveness of the intervention, the primary outcome measures will be evaluated both as a continuous outcome and as a logistic outcome evaluating the proportion of students below a given threshold. All analyses will be performed according to the intention-to-treat principle, and supplemented with exploratory analyses to test associations between outcome measures and implementation fidelity using data from the process analyses. Because of the cluster structure of the data, random effects for school and class will be included in all analyses.

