### RCT phase

*The randomized controlled trial (*RCT) entails the implementation of the final intervention program (Table 1) in the selected settings. Based on statistical power calculations and the capacity of the research set-up, a target of 12 schools was set for both the control and the intervention group. Municipalities were selected based on maximizing geographic spread, difference in size and difference in allocated budget for public schools [32]. Municipalities were not contacted if they already had large scale school development projects; were located near universities or university colleges other than the operating unit (University of Southern Denmark); located in relatively hard to reach locations; or had less than 6 schools in the entire school district. Based on initial screening, 11 of 98 Danish municipalities were contacted. After consent, local authorities initiated the first contact with schools or gave the research team permission to contact the schools directly. The research team held individual meetings with all interested schools and a total of 24 schools were enrolled. A stratified randomization was then conducted with three strata and with the constraint of an even distribution of schools from each municipality in the intervention group and the control group respectively. The three strata were defined by school typology, based on school size and district socio-economic status. Stratum A: Small schools, <70 pupils in grades 4–6, often located in small rural villages; Stratum B: Larger schools, >70 pupils, with low socio-economic status; and Stratum C: Larger schools with high socio-economic status. Beginning with Stratum A, schools were randomly assigned to either intervention or comparison by means of simple randomization - while adhering to the constraint of even distribution of schools from the various municipalities in the intervention and control group.

The initial part of the RCT phase is illustrated in Fig. 3.

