## Discussion

Standing on the verge of the program evaluation phase, the developed school-based, physical activity intervention holds some promising strengths, as well as considerations. These will be summarized and discussed in the following section.

First of all, the intervention focuses on the mental benefits of physical activity at school, which has been a rather neglected theme in health promotion research during recent decades. This is unfortunate. Mental health has been proclaimed as one of the most important health concerns of the 21^st^ century, as stated early on by WHO in their 2004 summary report, *Promoting Mental Health*. On top of this the mutually dependent relationship between physical activity and mental health has not yet been fully uncovered [1, 56].

Another characteristic feature of the study is the cluster RCT study design, which evaluates the real-world effectiveness of an intervention. 24 schools were randomized and the total study population consists of 3124 children (baseline), who are followed over a period of 9 months. To our knowledge, this makes it one of the largest physical activity intervention projects promoting psychosocial well-being among children and youths.

Alongside the comprehensive effectiveness evaluation, the study is designed to gain knowledge on a broad variety of implementation issues. This knowledge will be highly usable for educators, school managers and policy makers when tackling, for instance local challenges regarding school-based PA.

The detailed information on project delivery and roll-out at the school level makes it possible to better inform future practice. This study is co-created with and delivered by educators and school managers, which ensures that the findings and experiences are particularly relevant for practice.

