There are considerations within the study, which must be taken into account. Firstly, the measurement of psychosocial well-being relies on data generated via survey tools, which can only grasp parts of this complex phenomenon. Secondly, the multi-component design makes it difficult to single out the effectiveness of, for instance, individual PA activities. Thirdly, although 3124 pupils and nine months follow-up are considered a comprehensive design, there is still limited power to detect a real intervention effect. Facilitating and detecting robust improvements in psychosocial well-being among children and youths via PA may very well take years instead of months. Fourthly, the intervention has to be balanced between tailoring the intervention to the individual school and ensuring a certain degree of comparability. Too much tailoring could lead to a non-comparable intervention and too much conformity could entail lower motivation for implementation among key stakeholders.

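### The 0.09 detectable difference treats 72 classes per arm as independent clusters although 12 schools per arm were randomised, so the stated power calculation contains no between-school term

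*Protocol article*

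**What the plan says.** In the Protocol article, section RCT phase, the unit of allocation is the school: "schools were randomly assigned to either intervention or comparison by means of simple randomization", within three strata and balanced by municipality. The same section says that "a target of 12 schools was set for both the control and the intervention group", and gives statistical power together with research capacity as the reason.

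The section Statistical considerations opens by acknowledging clustering by class, school and surroundings, and then says: "This internal variation at school and class level was accounted for in the sample size calculations". The calculation follows: "With a mean of 3.12, an SD of 0.70, a significance level of 0.05, a statistical power of 0.80", with "an ICC of 0.025 at school-class level, 72 classes from 12 schools on each arm and approximately 20 pupils in each class". The result is that "it will be possible to detect a difference of 0.09", that is, a rise from 3.12 to 3.21. One ICC and one cluster size are given. The section also plans random effects for both school and class in all analyses, and lists the baseline outcome among the adjustment factors.

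The Discussion remarks that "there is still limited power to detect a real intervention effect", in connection with the number of pupils and the nine-month follow-up.

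**The concern.** In a cluster trial the power calculation has to carry the correlation among pupils at the level that was randomised. Here each randomised unit is a school of about six classes. If pupils in different classes of one school resemble each other at all, those six classes are not six independent pieces of information about the intervention. A calculation that counts 72 clusters per arm, when 12 were allocated, then gives too small a standard error.

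The phrase used for the ICC does not remove the difficulty. If 0.025 describes only the correlation within a class, the school term is missing. If it includes correlation between classes of the same school, those classes cannot be counted as independent clusters.

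At stake is the reading of the main result. The article presents 3.21 as the mean that must be reached for an effect to be detected, and power is part of the reason given for 12 schools per arm. A reader of a non-significant result may take 0.09 as a difference the trial had an 80% chance of finding.

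**Working it through.** **Inputs from the article.** SD 0.70; α 0.05 (taken as two-sided, since one-sided gives 0.079 and does not match); power 0.80; ICC 0.025; 12 schools and 72 classes per arm, hence k = 72/12 = 6 classes per school; m = 20 pupils per class, hence 120 per school and 72 × 20 = 1440 per arm.

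**Inputs not in the article, so assumed.** The correlation between pupils in different classes of the same school (ρ_school) is varied from 0 to 0.025. The correlation r between baseline and follow-up outcome is set at 0.6, with 0.7 as a comparison. Baseline adjustment is taken to reduce the variance by the factor 1 − r² at every level.

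**Step 1: reproduce the stated figure.** With the class as cluster:
- Design effect DE = 1 + (m − 1) × ICC = 1 + 19 × 0.025 = 1.475.
- SE = 0.70 × √(2 × 1.475 / 1440) = 0.0317.
- Detectable difference = (1.960 + 0.842) × 0.0317 = 0.0888, which rounds to 0.09. Power for 0.09 is 81%.

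Other readings do not give 0.09: ignoring clustering gives 0.073, and taking the school as cluster with ICC 0.025 gives 0.146. So the printed result is the class-level calculation.

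**Step 2: add the school term.** For pupils in classes in randomised schools,

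DE = 1 + (m − 1)ρ_class + m(k − 1)ρ_school = 1 + 19 × 0.025 + 100 × ρ_school.

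Here ρ_class = 0.025 is the total correlation within a class. With 24 schools the comparison has about 24 − 2 = 22 degrees of freedom. Under the noncentral t with 22 df, the difference detectable at 80% power is 2.93 × SE (2.074 + 0.858).

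| Assumed ρ_school | DE | SE | Detectable difference, unadjusted | Power for 0.09, t with 22 df | Power for 0.09, normal |
|---|---|---|---|---|---|
| 0 | 1.475 | 0.0317 | 0.093 | 77% | 81% |
| 0.005 | 1.975 | 0.0367 | 0.107 | 65% | 69% |
| 0.01 | 2.475 | 0.0410 | 0.120 | 55% | 59% |
| 0.025 | 3.975 | 0.0520 | 0.152 | 38% | 41% |

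The last row is the upper bound: all of the 0.025 lies between schools and classes add nothing. Using the actual baseline number (3124/24 ≈ 130 pupils per school) changes that row little: 0.151 and 39%.

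**Step 3: allow for the planned baseline adjustment.** With r = 0.6 each SE is multiplied by √(1 − 0.36) = 0.8 (t with 22 df):

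| Assumed ρ_school | Detectable difference, r = 0.6 | Power for 0.09 |
|---|---|---|
| 0 | 0.074 | 92% |
| 0.005 | 0.086 | 83% |
| 0.01 | 0.096 | 75% |
| 0.025 | 0.122 | 54% |

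With r = 0.7, power for 0.09 is 83.5% at ρ_school = 0.01 and 64% at 0.025.

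**Not included.** School sizes vary: Stratum A schools have fewer than 70 pupils in these grades, against a mean of about 130. This lowers power further by an amount that the article does not allow one to fix.

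**The case against.** The strongest reply is that the printed calculation errs in both directions. It omits the school term but also takes no credit for adjusting for the baseline outcome, which usually gains precision. Step 3 shows that the gain can be enough: with r = 0.6 the adjusted analysis exceeds 80% power for 0.09 at school ICCs of 0 and 0.005, and with r = 0.7 it does so at 0.01. Stratification by school size and socio-economic status, if modelled, could also remove some between-school variance. This stands. A reader might infer that the trial does not have its stated power, or that its true detectable difference is about 0.10 to 0.15. The article supports neither: it gives no school ICC and no baseline correlation, and that range is roughly the unadjusted one, whereas the planned analysis is adjusted.

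It can also be said that the planned models carry a school random effect, so the final inference will respect the design. That is right, and it confines the fault to the power statement. It also means that the power statement describes a different model from the one to be fitted.

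Finally, the Discussion concedes limited power, and the number of schools rested partly on capacity. The concession is general: it does not mention clustering and does not correct the 0.09. Nothing in the article says that a null result will be read as excluding 0.09; that is a risk for readers, not a stated intention.

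**Conclusion.** Wrong as written. The 0.09 at 80% power is arithmetically right for 72 independent classes per arm, but that is not the design, and the claim that school-level variation entered the calculation does not fit the printed inputs. On its own unadjusted terms the figure survives only if the school ICC is zero and large-sample critical values are used. Any positive school ICC weakens it, down to 38% power and a detectable difference of 0.152 at the upper bound. These sizes rest on equal schools of 6 × 20 pupils, a within-class correlation of 0.025, and school ICCs that are assumed.

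The power of the planned baseline-adjusted analysis remains open. It may lie above or below 80% for 0.09, depending on two quantities that the article does not report.

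**What to change.** Replace the power statement with one that takes the school as the randomised unit:

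- Use DE = 1 + (m − 1)ρ_class + m(k − 1)ρ_school with about 22 degrees of freedom.
- Give separate school and class ICCs, estimated from the baseline data of the 24 schools, pooled and without any comparison of arms.
- Allow for the actual variation in school size.
- State the baseline-outcome correlation that is assumed, with its source, so that the power refers to the adjusted model.
- Report whatever detectable difference results in place of 0.09, without fixing a range beforehand.
- Reword the sentence on school and class variation so that it describes what the calculation contains.

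The cost is one recalculation and one revised paragraph. No schools are added, and data collection and the analysis model stay as they are. The restated difference may turn out less favourable than 0.09.
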